#### Borg Rating of Perceived Exertion

Perceived exertion was measured according to the Borg Rating of Perceived Exertion scale [27] in each exercise with a score ranging from 6 to 20.

#### Maximum Oxygen

A respiratory gas analysis device, or metabolic gas analyzer device, is used to measure the maximum oxygen consumption during the physical activity on a treadmill or bicycle at different intensities. Queen’s step test was used to calculate the VO_2_ max (for females) according to the following formula [28]:

VO_2_ max (ml/kg/min) = 65.81 – [0.1847 × pulse rate beats (for 15 seconds)/min]

#### Muscle Preparation Test

Before the daily muscle preparation test, participants were guided through a 5-minute dynamic warm-up. The warm-up session began with a short walk to an indoor track or open gym. Next, a series of active movements targeting the pectoral, deltoid, and trapezius muscles was completed. Muscle tests included those indicated in the ACSM Health-Related Fitness Assessment Guide [29], such as the plank test (in seconds), the number of correct push-ups performed within 1 minute, and the wall squat test (how long the participant remains in squat position until fatigue). The participant is instructed to rate the pain intensity in their legs on a 0-10 numerical rating scale, with 0 defined as “no pain” and 10 as “the worst imaginable pain” [30].

#### Balance of Energy Expenditure and Energy Intake

Energy intake was recorded for each participant with daily energy intake obtained using the dietary analysis software Nutrition 4, version 1 [31].

#### Metabolic Syndrome

The siMS score was calculated as a measure of metabolic syndrome according to the following formula [32]:

siMS score = [(2 × waist circumference)/height] + glucose/reference value + triglycerides/reference value + systolic blood pressure/reference value – HDL/reference value

The siMS risk score was calculated as an expansion of the siMS score using the following formula:

siMS score × (age/50) × (family history of cardio- or cerebrovascular event=1.2, else=1)

#### Appetite and Nutrition

To assess subjective appetite sensations, the visual analog scale (VAS) is used. A VAS is typically composed of lines (of varying length) with words anchored at each end describing the extremes (ie, “I have never been hungrier” to “I am not hungry at all”). Participants are then asked to make a mark across the line corresponding to their feelings [33].

Nutrition attitude will be measured using the EAT-26 tool, a 26-item scale that assesses the symptoms and characteristics of eating disorders and yields an overall score. This questionnaire asks about the frequency of thinking and feeling about food, eating, and their body in disordered ways. Items are rated on a 6-point Likert scale, ranging from “always” to “never.” The three least symptomatic responses (never, rarely, and sometimes) are given a value of 0. A Cronbach α of 0.94 was reported for the EAT-26 in a sample of women [34]. A score of 20 or higher is considered to indicate the likelihood of having an eating disorder. EAT-26 has been validated by factor analysis in an Iranian population, which is based on three response options (never, rarely, and sometimes), and the Cronbach α was reported to be 0.86 [35].

### Standard-Calorie-Expenditure Training Protocol

According to the ACSM fitness guidelines [36], the standard-calorie-expenditure program includes 15 minutes of walking or running on a treadmill and 24 minutes of whole-body exercises in the first 4 weeks, followed by 25 minutes of walking and running and 39 minutes of whole-body exercises in the last 4 weeks. Specifically, this program involves 12 weeks of multimodal training starting with 3 weekly sessions of 30 minutes of compound training at a moderate intensity of 60%-75% VO_2_ max with 900 kilocalories of energy expenditure per week. By the end of the exercise period, the energy expenditure increases to 1200 kilocalories per week, with the exercise period increasing to 75 minutes with an intensity of 75% VO_2_ max. The details of the program are outlined in Table 2.

**Table 2 table2:** Exercise protocol in the standard-calorie-expenditure group on a weekly and session basis (3 sessions/week).

Parameter			Week 1		Week 2		Week 3		Week 4		Week 5		Week 6		Week 7		Week 8		Week 9		Week 10		Week 11		Week 12
Total time (min)			120		120		120		120		155		155		155		155		190		190		190		190
EXE^a^ (min)			15		15		15		15		20		20		20		20		25		25		25		25
MHR^b^, %			65-75		70-85		65-75		70-85		65-75		70-85		65-75		70-85		65-75		70-85		65-75		70-85

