## Methods

### Study Design

This study was designed to assess the effect of a 12-week multimodal exercise program intervention under two different calorie-expenditure conditions (high=3000 calories/week vs standard=1200 calories/week) and a no-exercise waitlist control group. The study was conducted at the University of Tabriz in the southeastern region of Azerbaijan, Iran. This study was registered in the Iranian Registry of Clinical Trials (IRCT20220202053916N1).

Figure 1 summarizes the proposed 12-week training plan. Participants will be allocated to three groups: a high-calorie-expenditure group, standard-calorie-expenditure group, and control group. In the high-calorie-expenditure group, participants will engage in 3 sessions of exercise per week for 45 minutes with an estimated expenditure of 650-900 calories per week for weeks 1 and 2. In the third week, they will also have 3 sessions per week with a training duration of 50 minutes per session at an estimated calorie expenditure of 750-1200 per week. In the fourth week, the duration of the exercise will be increased to 60 minutes with 3 sessions per week, thereby increasing the calorie expenditure of the exercise by approximately 1200-1300 per week. In the fifth and sixth weeks, the training time will increase to 70 minutes and the number of training sessions will also increase to 4 sessions per week, resulting in calorie expenditure of approximately 1800-1500 and 1600-2000 calories per week, respectively. In week 7, the training duration will increase to 4 sessions of 80 minutes each with estimated weekly calorie expenditure of 1800-2200. In weeks 8 and 9, the training duration will increase to 90 minutes with expenditure of 1900-2500 calories/week. In the last 3 weeks, the number of sessions will reach 5 with weekly sessions of 95, 100, 110, 110, and 110 minutes, respectively accounting for 2700-3100, 3000-3500, and 3300-3700 calories consumed in week 10, 11, and 12, respectively.

The standard-calorie-expenditure group will receive a 12-week exercise program in the form of 3 training sessions. In weeks 1 to 4, each session will comprise 40 minutes of exercise with 650-900 calories consumed per week; in weeks 5 to 8, sessions will last 60 minutes with 1000-1200 calories consumed per week; and weeks 9 to 12 will involve an increase in the training time to 80 minutes with expenditure of 1200-1500 calories per week.

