**Whole-body exercises: 10 movements^c^**																									
	EXE time (min)	24		24		24		24		31.5		31.5		31.5		31.5		39		39		39		39	
	Sets (rest), seconds	3 (30)		3 (30)		3 (30)		3 (30)		3 (30)		3 (30)		3 (30)		3 (30)		3 (30)		3 (30)		3 (30)		3 (30)	
	Work (rest), seconds	30 (15)		30 (15)		30 (15)		30 (15)		40 (20)		40 (20)		40 (20)		40 (20)		50 (25)		50 (25)		50 (25)		50 (25)	
RPE^d^			13-15		14-16		13-15		1416		13-15		14-16		13-15		14-16		13-15		14-16		13-15		14-16
Calories/session			220-280		230-290		260-300		260-320		320-390		330-410		350-420		360-440		370-480		375-490		370-480		400-500
Total calories/week			650-850		700-900		780-900		800-950		920-1185		950-1200		100-1300		110-1340		115-1440		120-1470		115-1440		120-1500

^a^EXE: aerobic exercise.

^b^MHR: maximum heart rate.

^c^In the whole-body section, 10 movements are performed in 3 sets, which increases based on the addition of long-term load and training volume, including a change in resting interval intensity (active recovery and low intensity/recovery such as jogging). Based on the timing of the table, in the range between each set, there is a constant passive recovery period of 30 seconds.

^d^RPE: rate of perceived exertion; calculated as the maximal effort movement for each subject in 30 seconds based on a minimum of 6 when at rest and 20 at the maximum heart rate. During the initial session, we determined the RPE to range from 13 to 15.

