### High-Calorie-Expenditure Training Protocol

Compared to the standard program, the exercise prescription for the high-calorie-expenditure group has a longer duration (45-110 vs 40-65 minutes per session), lower intensity (50%-75% vs 60%-85% VO_2_ max), and more frequent exercise (5 vs 3 times a week). Walking and running are the preferred forms of exercise to maximize calorie burning in comparison to weight training (cycling or rowing), which burns fewer calories. In the high-calorie-expenditure group, the goal of exercise expenditure is 3000-3500 kilocalories per week [30], which is achieved after 2-4 weeks of gradual lengthening of the exercise periods. The training protocol also lasts for 12 weeks, with 45 minutes of whole-body training at 65%-85% VO_2_ max consuming 1200 kilocalories per week; based on the principle of gradual overload with increasing weight, the energy expenditure at the end of the training period will be 3500 kilocalories. The calories increase per week [37] and the training time increases to 112 minutes. The main element of training is the same as that of the standard protocol, which starts with 3 sessions per week and gradually increases to 5 sessions per week, although the duration of each training session will be twice that for the standard-calorie-expenditure program in each step (Table 3).

In addition, the participants will be taught how to measure their heart rate in 10 seconds using the two index and middle fingers to find the pulse of the carotid artery of the neck and the pulse of the wrist. Participants will report their heart rate during aerobic exercise when requested by the investigator [38]. After 1 minute of active rest, each participant will begin a full-body exercise.

**Table 3 table3:** High-calorie-expenditure training protocol on a weekly and session basis (3 sessions/week).

Parameter			Week 1		Week 2		Week 3		Week 4		Week 5		Week 6		Week 7		Week 8		Week 9		Week 10		Week 11		Week 12
Total time (min)			135		135		150		150		246		280		340		340		475		525		530		530
EXE^a^ (min)			20		20		20		30		30		30		40		40		40		50		50		50
MHR^b^, %			65-75		70-85		65-75		70-85		65-75		70-85		65-75		70-85		65-75		70-85		65-75		70-85

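### The standard (comparator) arm's planned session length is stated in three incompatible versions, differing by up to 26% in weekly minutes between Study Design and Table 2

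*Protocol article*

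**What the plan says.** The standard arm trains three times a week for 12 weeks. Its session length appears in four places.

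- **Study Design.** "In weeks 1 to 4, each session will comprise 40 minutes of exercise with 650-900 calories consumed per week"; then "in weeks 5 to 8, sessions will last 60 minutes with 1000-1200 calories consumed per week"; then "weeks 9 to 12 will involve an increase in the training time to 80 minutes with expenditure of 1200-1500 calories per week".
- **Standard-Calorie-Expenditure Training Protocol, prose.** The programme is described as "starting with 3 weekly sessions of 30 minutes of compound training at a moderate intensity", "with 900 kilocalories of energy expenditure per week", and ends at 1200 kcal per week "with the exercise period increasing to 75 minutes with an intensity of 75% VO_2_ max". The sentence before this gives the session's components: 15 minutes of treadmill work plus 24 of whole-body exercise in the first four weeks, and 25 plus 39 in the last four.
- **Table 2.** Total time is 120, 155 and 190 minutes per week by four-week block, at three sessions per week. Weekly calories start at 650-850. For weeks 7 to 10 the row reads "100-1300 110-1340 115-1440 120-1470", followed by 115-1440 and 120-1500 for weeks 11 and 12.
- **High-Calorie-Expenditure Training Protocol.** The high arm is contrasted with the standard arm as having a "longer duration (45-110 vs 40-65 minutes per session". The same section says that high-arm sessions last twice as long as the standard ones at each step.

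**The concern.** Aim 3 compares the high-expenditure programme with the standard one, so the standard prescription is one side of the trial's main contrast. A reader who wants to know what that side was meant to be finds different answers in Study Design, in the training-protocol prose and in Table 2.

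Two other parts of the plan lean on this prescription. Under Intervention Fidelity, an independent assessor checks classes against the explicit components of the protocol, and with three versions there is no single reference. The high arm's session length is also described as a multiple of the standard arm's, so the ambiguity carries into the other arm.

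**Working it through.** **1. Does Table 2 agree with itself on time?** The inputs are its work and rest rows: 10 movements, 3 sets, work + rest of 45, 60 and 75 seconds by block, and 30 seconds after each set.

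- Weeks 1-4: (10 × 3 × 45 + 3 × 30)/60 = 24 min
- Weeks 5-8: (10 × 3 × 60 + 3 × 30)/60 = 31.5 min
- Weeks 9-12: (10 × 3 × 75 + 3 × 30)/60 = 39 min

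These reproduce the table's whole-body times. Adding aerobic time (15, 20, 25) gives 39, 51.5 and 64 min. The one-minute rest between the two parts, described in the section on a single training session, brings these to 40, 52.5 and 65. The total-time row divided by 3 gives 40.0, 51.7 and 63.3. Table 2, the prose components (39 and 64) and the 40-65 range therefore agree to within about two minutes and count as one version.

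**2. The versions side by side (minutes per session)**

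| Source | Weeks 1-4 | Weeks 5-8 | Weeks 9-12 |
|---|---|---|---|
| Study Design | 40 | 60 | 80 |
| Training-protocol prose | 30 at start | not given | 75 at end |
| Table 2 (components and 40-65 range agree) | 40.0 | 51.7 | 63.3 |

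**3. Size of the gap**

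- Weeks 9-12: 3 × 80 = 240 against 190 min/week; 50/190 = 26%.
- Weeks 5-8: 3 × 60 = 180 against 155 min/week; 25/155 = 16%.
- Whole programme: 3 × 4 × (40 + 60 + 80) = 2160 against 4 × (120 + 155 + 190) = 1860 min; 300/1860 = 16%.
- Prose against Table 2: 3 × 30 = 90 against 120 min/week at the start; 3 × 75 = 225 against 190 at the end.

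**4. Could warm-up and cool-down explain it?** Study Design minus Table 2 is 0, 8.3 and 16.7 minutes per session across the three blocks. A fixed addition would give the same difference in each block.

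**5. The doubling statement.** Twice the final standard session is 127 (Table 2), 150 (prose) or 160 minutes (Study Design). The high arm's stated maximum is 110 minutes in the comparison and 112 in the prose. No version of the standard arm yields it.

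**6. Energy (lesser point).** The prose start of 900 kcal/week is 50 above the top of Table 2's week 1 range (650-850). Table 2's session row × 3 agrees with its weekly row to within about 4% in weeks 1-6. From week 7 only the lower limits break:

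| Week | Session row × 3 | Weekly row as printed |
|---|---|---|
| 7 | 1050-1260 | 100-1300 |
| 8 | 1080-1320 | 110-1340 |
| 9 | 1110-1440 | 115-1440 |
| 10 | 1125-1470 | 120-1470 |
| 11 | 1110-1440 | 115-1440 |
| 12 | 1200-1500 | 120-1500 |

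Each printed lower limit is below the energy of one session in its own column (350 kcal or more). With a final zero restored, they read 1000, 1100, 1150, 1200, 1150 and 1200, within about 7% of the session row × 3. The upper limits already agree within about 3%.

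**The case against.** The best defence is that a coherent schedule does exist. Table 2 can be rebuilt from its own rows, two other statements agree with it, and the training-protocol section refers the reader to it for details. That stands, and it is why the count is three versions, not five. It does not remove the conflict: Study Design sets out its own explicit block-by-block schedule, and nothing in the article says which takes precedence.

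A second defence is that the arms are defined by weekly energy, and the energy statements mostly overlap: 900 is the top of Study Design's 650-900 for weeks 1-4, and 1200 is the bottom of its 1200-1500 for weeks 9-12. This also stands, and it keeps energy a lesser point.

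Two stronger readings are tempting. A reader might infer that weekly floors of 100-120 kcal let almost any attendance count as on target. The article contains no calorie-based compliance rule. Study Population excludes on missing more than 30% of sessions, and fidelity is checked by checklist and class logs. The floors look like a printing or text-extraction loss; the same table shows one exertion range without its hyphen. Any calorie gap computed from them would only measure the misprint.

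A reader might also infer that the delivered dose is unknown. Energy is measured by watch in every exercise session, and the comparison with prior studies reports 450 kcal per session and 1350 overall for the standard arm (3 × 450 = 1350). Those figures bear on energy delivered. They do not show which planned session length was used, and the Results section describes the same arm as reaching up to 1200 per week.

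**Conclusion.** The point holds for planned session length. The comparator's prescription is stated in three versions that cannot all be true. The largest weekly gap between Study Design and Table 2 is 26% (weeks 9-12), with 16% over the whole programme. The prose conflicts both with the components in the sentence before it and with the table it introduces. The calculation assumes three sessions per week throughout, which Study Design, the prose and the Table 2 caption all state.

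The energy discrepancies are minor: one starting value 50 kcal outside its range, and six lower limits that appear to lack a final zero. The sample-size calculation is unaffected. These are figures that the article states and contradicts, not details left to a fuller document. The correction should be made because the comparator defines aim 3 and serves as the fidelity reference. Which schedule is right cannot be settled from the document, and no view is taken.

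**What to change.** Reconcile Study Design, the Standard-Calorie-Expenditure Training Protocol prose, Table 2 and the comparison in the High-Calorie-Expenditure Training Protocol to one week-by-week standard-arm schedule giving sessions, minutes per session, kcal per session and kcal per week. Say whether warm-up, cool-down and rest are counted in the minutes. Check the schedule against the instructors' class logs, and have the sponsor state which version was used.

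Make Table 2's session and weekly calorie rows consistent for weeks 7-12, and reconcile the prose starting energy with week 1. Use the resulting schedule as the fidelity reference and as the base for the doubling statement, which must itself be reconciled with the high arm's stated session lengths.

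The cost is a text and table correction plus a check of existing logs. No new data are needed.

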**Whole-body exercises: 10 movements^c^**																									
	EXE time (min)	24		24		24		24		31.5		31.5		31.5		31.5		39		39		39		39	
	Sets (rest), seconds	3 (30)		3 (30)		3 (30)		3 (30)		3 (30)		3 (30)		3 (30)		3 (30)		3 (30)		3 (30)		3 (30)		3 (30)	
	Work (rest), seconds	30 (15)		30 (15)		30 (15)		30 (15)		40 (20)		40 (20)		40 (20)		40 (20)		50 (25)		50 (25)		50 (25)		50 (25)	
RPE^d^			13-15		14-16		13-15		1416		13-15		14-16		13-15		14-16		13-15		14-16		13-15		14-16
Calories/session			220-280		230-290		260-300		260-320		320-390		330-410		350-420		360-440		370-480		375-490		370-480		400-500
Total calories/week			650-850		700-900		780-900		800-950		920-1185		950-1200		100-1300		110-1340		115-1440		120-1470		115-1440		120-1500

^a^EXE: aerobic exercise.

^b^MHR: maximum heart rate.

^c^In the whole-body section, 10 movements are performed in 3 sets, which increases based on the addition of long-term load and training volume, including a change in resting interval intensity (active recovery and low intensity/recovery such as jogging). Based on the timing of the table, in the range between each set, there is a constant passive recovery period of 30 seconds.

^d^RPE: rate of perceived exertion; calculated as the maximal effort movement for each subject in 30 seconds based on a minimum of 6 when at rest and 20 at the maximum heart rate. During the initial session, we determined the RPE to range from 13 to 15.

### High-Calorie-Expenditure Training Protocol

Compared to the standard program, the exercise prescription for the high-calorie-expenditure group has a longer duration (45-110 vs 40-65 minutes per session), lower intensity (50%-75% vs 60%-85% VO_2_ max), and more frequent exercise (5 vs 3 times a week). Walking and running are the preferred forms of exercise to maximize calorie burning in comparison to weight training (cycling or rowing), which burns fewer calories. In the high-calorie-expenditure group, the goal of exercise expenditure is 3000-3500 kilocalories per week [30], which is achieved after 2-4 weeks of gradual lengthening of the exercise periods. The training protocol also lasts for 12 weeks, with 45 minutes of whole-body training at 65%-85% VO_2_ max consuming 1200 kilocalories per week; based on the principle of gradual overload with increasing weight, the energy expenditure at the end of the training period will be 3500 kilocalories. The calories increase per week [37] and the training time increases to 112 minutes. The main element of training is the same as that of the standard protocol, which starts with 3 sessions per week and gradually increases to 5 sessions per week, although the duration of each training session will be twice that for the standard-calorie-expenditure program in each step (Table 3).

In addition, the participants will be taught how to measure their heart rate in 10 seconds using the two index and middle fingers to find the pulse of the carotid artery of the neck and the pulse of the wrist. Participants will report their heart rate during aerobic exercise when requested by the investigator [38]. After 1 minute of active rest, each participant will begin a full-body exercise.

**Table 3 table3:** High-calorie-expenditure training protocol on a weekly and session basis (3 sessions/week).

Parameter			Week 1		Week 2		Week 3		Week 4		Week 5		Week 6		Week 7		Week 8		Week 9		Week 10		Week 11		Week 12
Total time (min)			135		135		150		150		246		280		340		340		475		525		530		530
EXE^a^ (min)			20		20		20		30		30		30		40		40		40		50		50		50
MHR^b^, %			65-75		70-85		65-75		70-85		65-75		70-85		65-75		70-85		65-75		70-85		65-75		70-85

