**Methods:**

This is a randomized controlled trial with a pretest-posttest design. Participants include 33 women with a BMI in the overweight range (25-29.9) allocated to three groups: two intervention groups and one control group. The intervention will be conducted for 12 weeks. Participants in the first group will be assigned an exercise program with high energy expenditure of approximately 3000-3500 kilocalories/week in the form of 5 sessions per week with an intensity of 50%-75% maximum oxygen rate (VO_2_ max) and 60%-80% target heart rate. The second group will be assigned an exercise program with a standard energy expenditure of approximately 1200-1500 kilocalories/week with 3 sessions per week at an intensity of 60%-75% VO_2_ max, according to The American College of Sports Medicine guideline. The effects of the multimodal training program with daily tasks will be compared to those of the standard-calorie-expenditure and control (no exercise) conditions with respect to changes in glycemic indices and body composition. Daily calories will be calculated through the International Physical Activity Questionnaire and using Nutrition 4 software.

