**Whole-body exercises: 10 movements^c^**																									
	EXE time (min)	25		25		30		30		40		40		45		45		55		55		60		60	
	Sets (rest, seconds)	3 (30)		3(30)		3(30)		3(30)		3(30)		3(30)		3(30)		3(30)		3(30)		3(30)		3(30)		3(30)	
	Work (rest), seconds	30 (15)		30 (15)		40 (20)		40 (20)		50 (25)		50 (25)		60 (30)		60 (30)		70 (35)		70 (35)		80 (40)		80 (40)	
RPE^d^			13-15		14-16		13-15		14-16		13-15		14-16		13-15		14-16		13-15		14-16		13-15		14-16
Calories/session			250-370		320-400		390-400		400-500		450-560		500-580		580-660		600-680		620-700		250-370		320-400		390-400
Total calories/week			750-1100		950-1200		1170-1200		1200-1500		1800-2000		2000-2200		2300-2600		2400-2700		3000-3200		3200-3500		3700-3900		3800-4000

^a^EXO: aerobic exercise.

^b^MHR: maximum heart rate.

^c^In the whole-body section, 10 movements are performed in 3 sets, which increases based on the addition of long-term load and training volume, including a change in resting interval intensity (active recovery and low intensity/recovery such as jogging). Based on the timing of the table, in the range between each set, there is a constant passive recovery period of 30 seconds.

^d^RPE: rate of perceived exertion; calculated as the maximal effort movement for each subject in 30 seconds based on a minimum of 6 when at rest and 20 at the maximum heart rate. During the initial session, we determined the RPE to range from 13 to 15.

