### Comparison With Prior Studies

In the case of severe and acute illnesses such as COVID-19, the effects of the disease not only decrease physical activity but also cause obesity problems in women [40]. Consequently, living an active lifestyle and monitoring one’s diet by counting daily calories can be a helpful approach to lose weight. The preliminary results of this study show that the average calorie expenditure of group-based mixed high-calorie-expenditure exercise (including the warm-up and cool-down periods) was 800 kilocalories, as estimated by the Apple Watch calorimeter. By contrast, the energy consumption per session for the standard-calorie-expenditure group was only 450 kilocalories. Results from a limited number of studies measuring energy expenditure with caloric intake have been mixed. Overall, participants performing high- and standard-calorie-expenditure exercises burned 3700 and 1350 calories, respectively. Brisebois [41] showed that 30 adults (19-60 years old, 50% women) had an average energy expenditure of 7.5 kilocalories/minute in a 60-minute CrossFit session. In a 2018 study [42], a 10-month implementation of an integrated neuromuscular circuit-type training program in small groups resulted in (1) an increase in daily energy expenditure relative to energy intake, leading to a decrease in body mass and fat; (2) an increase in strength and cardiovascular performance; and (3) a high adherence rate. Exercise-induced gains were reduced but not lost after a 5-month no-exercise period. The exercise program involved noninjury HIIT using resistance exercises of the whole body and cardiovascular activities with a limited time commitment and organized in a small group, resulting in favorable adaptation in the body and fat mass of people with overweight and obesity. Circuit-type neuromuscular exercise training protocols using only body-weight exercises could reduce body mass and fat and improve strength and endurance performance in women. These changes were attributed to an increased resting metabolic rate and lean mass, leading to increased energy expenditure. Weight/fat recovery from nonexercise was limited, suggesting that this type of exercise training may promote the long-term maintenance of weight loss in adults with overweight [42]. Willis et al [43] recorded the energy expenditure of 20 men and women during a 40-minute training session delivered by video. The findings indicated that the participants burned an average of 392 kilocalories per session (9.8 kilocalories per minute). Differences in the type and intensity of exercise throughout the session can explain the differences in the results of our study and those of previous studies. In addition, Willis et al [43] found a significant difference in energy expenditure between men and women of ~134 kilocalories per session (3 kilocalories/minute). This previous study compared the traditional exercise method with other methods. Therefore, it was not based on whole-body training and the sessions all involved steady-state exercise at the same intensity. Weight training is usually performed at high intensity for short periods with longer periods in between, which is expected. In this study, the timing of the training protocols was modified, but the protocol was similar to that of resistance training.

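### The planned weekly energy dose of the high-calorie arm is stated in conflicting ways, and neither weekly schedule averages the 3000-3500 kcal that labels the arm

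*Protocol article*

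**What the plan says.** The abstract describes the high-calorie arm as "high energy expenditure of approximately 3000-3500 kilocalories/week in the form of 5 sessions per week" and mentions no build-up. Study Design labels the two exercise arms "high=3000 calories/week vs standard=1200 calories/week".

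The High-Calorie-Expenditure Training Protocol section states that "the goal of exercise expenditure is 3000-3500 kilocalories per week [30], which is achieved after 2-4 weeks of gradual lengthening". The same paragraph says that "the energy expenditure at the end of the training period will be 3500 kilocalories".

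Two weekly schedules follow these labels. The Study Design text begins with "3 sessions of exercise per week for 45 minutes with an estimated expenditure of 650-900 calories per week for weeks 1 and 2" and ends with "2700-3100, 3000-3500, and 3300-3700 calories consumed in week 10, 11, and 12, respectively". Table 3, in its row "Total calories/week", runs from 750-1100 in week 1 to 3800-4000 in week 12.

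Among the early results, the Discussion says that "participants performing high- and standard-calorie-expenditure exercises burned 3700 and 1350 calories, respectively", without giving the period. It also gives an average of 800 kcal per session for the high-calorie arm. The Results section gives more than 3500 per week for that arm and up to 1200 for the standard arm.

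**The concern.** Weekly exercise energy is what separates the two exercise arms, so it is the randomised contrast. If the article gives several incompatible accounts of it, a reader cannot tell which programme was planned, cannot replicate it, and cannot judge achieved expenditure against a plan.

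The headline label also invites readers to tie any weight loss to roughly 3000-3500 kcal in each of 12 weeks, or in all but the first few. Neither schedule plans that.

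**Working it through.** **Inputs.** Weekly ranges in kcal for the high-calorie arm. Two readings of the Study Design text are assumed: its week 5 range, printed in reverse order, is taken as 1500-1800, and its week 4 figure is taken as the weekly level.

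| Week | Study Design text | Table 3 | Midpoints | Ranges overlap? |
|---|---|---|---|---|
| 1 | 650-900 | 750-1100 | 775 / 925 | yes |
| 2 | 650-900 | 950-1200 | 775 / 1075 | no |
| 3 | 750-1200 | 1170-1200 | 975 / 1185 | yes |
| 4 | 1200-1300 | 1200-1500 | 1250 / 1350 | yes |
| 5 | 1500-1800 | 1800-2000 | 1650 / 1900 | at 1800 only |
| 6 | 1600-2000 | 2000-2200 | 1800 / 2100 | at 2000 only |
| 7 | 1800-2200 | 2300-2600 | 2000 / 2450 | no |
| 8 | 1900-2500 | 2400-2700 | 2200 / 2550 | yes |
| 9 | 1900-2500 | 3000-3200 | 2200 / 3100 | no |
| 10 | 2700-3100 | 3200-3500 | 2900 / 3350 | no |
| 11 | 3000-3500 | 3700-3900 | 3250 / 3800 | no |
| 12 | 3300-3700 | 3800-4000 | 3500 / 3900 | no |

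**Can the label be reproduced?** Only as a late-phase value. The last three weeks in Study Design average (2900 + 3250 + 3500)/3 = 3217. The last four in Table 3 average (3100 + 3350 + 3800 + 3900)/4 = 3538, just above the label's upper end.

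**Twelve-week means of midpoints.**
- Study Design: 23275/12 = 1940.
- Table 3: 27685/12 = 2307.
- With every upper limit: 25600/12 = 2133 and 29100/12 = 2425.
- Leaving out weeks 1-4, the longest build-up the text allows: 19500/8 = 2438 and 23150/8 = 2894.

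All of these are below 3000.

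**Disagreement between the schedules.** Table 3's midpoint is higher in every week, by 100 (week 4) to 900 (week 9). The end-of-training figure of 3500 lies inside Study Design's week 12 range and outside Table 3's.

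**Table 3 against itself.** Its calories/session entries for weeks 10-12 (250-370, 320-400, 390-400) repeat those for weeks 1-3. At 5 sessions they give 1250-1850, 1600-2000 and 1950-2000. The stated totals are 3200-3500, 3700-3900 and 3800-4000.

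**Table 2 (standard arm) against itself.** The weekly lower limits for weeks 7-12 are printed as 100, 110, 115, 120, 115 and 120. Three times the session lower limits gives 1050, 1080, 1110, 1125, 1110 and 1200.

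**Contrast between arms.**
- Standard arm, Study Design: (4 × 775 + 4 × 1100 + 4 × 1350)/12 = 12900/12 = 1075.
- Standard arm, Table 2, as 3 × session midpoints: 12967.5/12 = 1081.
- Scheduled ratio: 1940/1075 = 1.80 (Study Design) and 2307/1081 = 2.13 (tables).
- Label ratio: 3000/1200 = 2.50, or 3250/1350 = 2.41 at the midpoints of the abstract's ranges.
- Scheduled gap: 1940 − 1075 = 865, or 2307 − 1081 = 1226 kcal/week, against 3250 − 1350 = 1900 on the label midpoints.

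**The case against.** The strongest reply is that the build-up is disclosed and the labels are end-of-programme targets. Study Design and Table 3 both show the progression, and the training section names 3500 as the final level. The standard arm is labelled in the same way: its 1200-1500 is the weeks 9-12 value, and its own mean of 1075 is 20% below the 1350 midpoint. This stands in part. The label is not a misstatement peculiar to the high-calorie arm. However, the abstract and the Study Design label carry no such limit, and the claim that the goal is met after 2-4 weeks cannot be squared with a final-phase target.

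Three stronger readings are tempting but not supported.

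- A reader might infer that the women received less than the article reports. The schedules are plans, and no 12-week mean of recorded expenditure is given, so this is not shown.
- A reader might say that the reported 800 kcal per session is impossible because Table 3's session row peaks at 700. That maximum depends on the weeks 10-12 entries that conflict with the table's own totals. Those totals divided by 5 give 640-700, 740-780 and 760-800, so 800 is within reach. The 800 also includes warm-up and cool-down. What remains is that a figure called an average equals the table's peak, while the scheduled means are 23275/47 = 495 and 27685/48 = 577 per session.
- A reader might infer that fidelity monitoring failed. The assessor's checklist covers content, and the article does not say that it scores calorie ranges.

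The Table 2 lower limits look like dropped digits and are minor on their own.

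**Conclusion.** The concern holds as an internal inconsistency in the planned dose. The 2-4 week statement is contradicted by both schedules and sits badly with the end-of-training statement in its own paragraph. The schedules do not overlap in 6 of 12 weeks, and their means are 35% and 23% below 3000 (40% and 29% below 3250). The lower limit reaches 3000 in only 2 or 4 weeks. The scheduled ratio between the exercise arms is about 1.8 or 2.1, against 2.4-2.5 on the labels.

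The means and ratios use range midpoints, the two readings of Study Design noted above and, for Table 2, the session row times three. The conclusion that both high-calorie means fall below 3000 does not depend on midpoints, because it also holds at every upper limit.

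The consequence is for how the contrast is described, interpreted and replicated. Nothing here affects allocation, power or the validity of the comparison as randomised.

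**What to change.** Reconcile the abstract, Study Design, both training-protocol sections and Tables 2 and 3 into one weekly schedule in which sessions, calories per session and weekly totals agree. This review takes no view on which figures are right.

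If the labels of both arms are final-phase targets, say so wherever they appear, and put the planned 12-week mean and cumulative energy beside them.

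Report recorded mean weekly and cumulative kcal per woman in each exercise arm, from the session data that the Calorie Expenditure section says are exported. State the period covered by the reported 3700, 1350, more than 3500 and 800 per session.

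The cost is corrected text and tables and a little summary work, with no new data collection. The drawback for the authors is a lower headline dose.
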